**Activities**
Traditional Chinese landscape painting and calligraphy and peer group participation
**Instruments used**
Pens, ink, paper, inkstones, and pigments
**Procedure and duration**
Preliminary understanding and familiarization (10 minutes)Creation of traditional Chinese landscape painting (25 minutes)Chinese calligraphy creation (15 minutes)Display and appreciation of artworks (5 minutes)Discussion of ongoing individual art activities (25 minutes)End of the intervention

#### Routine Care

As all 3 older adult centers operate under the same management, they follow the same schedules. These include daily activities such as basic limb exercises during specific activity hours from 8:30 AM to 10:30 AM and 2 PM to 4 PM. The Chinese art activities and Chinese art activities with peer group participation interventions are planned from 2 PM to 4 PM, whereas the control group will adhere to the original activity schedule of the older adult centers. All other everyday management and activities for the 3 groups will continue as normal.

### Outcomes

This research uses a repeated-measure design. In addition to the measurements obtained concurrently with the PWB assessment at baseline and 1 week after the intervention, further pre- and postintervention evaluations are performed for the happiness, relaxation, and loneliness scores and salivary cortisol levels. The schedule of evaluations is outlined in Table 1.

Demographic variables include age, gender, marital status, number of children, educational level, number of chronic diseases, type of residence (private or shared room), length of stay in the older adult center, frequency of monthly visits, and MMSE score.

The PWB score is assessed using the 18-item Chinese version of the PWB scale by Ryff [63]. This scale consists of 18 questions with 3 questions per dimension, covering a total of 6 dimensions: self-acceptance, positive relations with others, autonomy, environmental mastery, purpose in life, and personal growth.

The happiness, relaxation, and loneliness scores are measured using a specific 10-cm visual analog scale (VAS) [64-67]. After a decision is made, the recorded value is measured in millimeters (from left to right) using a ruler to assign a numerical value to the subjective evaluation, with possible scores ranging from 0 to 10. An example of the VAS is shown in Figure 4.

The VAS is a widely recognized and proven effective evaluation tool for subjective experience measurement in the older adult population [64,68-72]. However, studies have also shown that patients with cognitive decline, decreased hand flexibility, and impaired vision may find it difficult to complete, leading to unreliable results [71,73,74]. Therefore, the inclusion criteria stipulated requirements for MMSE scores higher than 24 and the ability to independently read and write. At the same time, the scale uses clearly marked and high-contrast black lines to ensure visual clarity, and during the first use, researchers will explain and demonstrate how to complete the scale to ensure that effective results are obtained from the participants.

**Figure 4. F4:**
[figure not shown]
Visual analog scale (VAS) for happiness.

Saliva will be collected 30 minutes before and following the intervention. We will use a saliva collecting tube. After collection, the saliva samples will be put on wet ice right away, brought to a laboratory within 3 hours, and frozen at −80 °C. Following the collection of all samples, the laboratory’s qualified researcher will be asked to conduct the salivary cortisol measurements on all the collected samples. The Jiangsu Provincial Department of Science and Technology has accredited the laboratory, and it has significant proficiency in measuring salivary cortisol levels. We will take the following measures to improve the effectiveness of cortisol measurement: (1) participants are instructed to avoid drinking alcohol for 12 hours, avoid eating for 1 hour, and avoid brushing their teeth for 10 minutes before collection; (2) all saliva samples are collected between 2 PM and 4 PM; and (3) samples contaminated with blood are excluded. The reference range for salivary cortisol is 2.09 to 22.63 nmol/L [75].

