**Figure 2. F2:**
[figure not shown]
The implementation phase and data collection procedures.

Outcome measures are gathered 30 minutes prior to and following each intervention session to assess immediate effects. A concluding follow-up assessment takes place 1 week after the final session to examine enduring outcomes. Figure 3 illustrates the research design within a single environment. The study protocol (version 1.0 dated March 2, 2026) complies with the SPIRIT (Standard Protocol Items: Recommendations for Interventional Trials) checklist (Table 1).

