**Procedure and duration**
Preliminary understanding and familiarization (10 minutes)Creation of traditional Chinese landscape paintings (25 minutes)Chinese calligraphy creation (15 minutes)

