#### Chinese Art Activities Combined With Peer Group Participation

The Chinese art activities with peer group participation intervention, supported by previous studies [51,61], consists of an 80-minute integrated session led by a single researcher (RA). On the basis of established recommendations that at least 4 participants are necessary for effective group interventions [62], the 10 participants in this arm are randomly divided into 2 groups of 5, each facilitated by 1 trained peer volunteer, resulting in 6 individuals per group including the peer volunteer.

Peer volunteers are recruited through self- and staff recommendation. The inclusion criteria are being aged over 60 years, having lived in the center for more than 6 months, having normal cognition, moving freely, having good communication skills, and being enthusiastic to participate. They are responsible for organizing and guiding participants to actively express themselves and encourage each other during the peer group participation phase. One week before the intervention begins, training on research objectives and intervention procedures is conducted through meetings. The training also includes researchers demonstrating communication skills such as organizing peer evaluations, encouraging expression, and strengthening practical abilities through simulated exercises and on-site guidance. The training simultaneously evaluates the competence of volunteers, screening qualified candidates to participate in subsequent interventions. This study will not provide financial compensation to peer volunteers. As an alternative, the research team will give them flowers.

The intervention begins with Chinese art activities that follow the established procedures. After the Chinese art activities are completed, peer group participation is immediately carried out. Peer volunteers organize members to showcase their works. They invite each member to elaborate on the significance of their work while promoting mutual appreciation among group members. Subsequently, participants are encouraged to exchange their works as gifts accompanied by handshakes, smiles, or nods. Finally, peer volunteers conclude the program by sharing personal stories highlighting adaptation to life at the older adult center. Textbox 2 contains information pertaining to the Chinese art activities and peer group participation interventional procedures.

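### Saliva 30 minutes before and after an 80-minute session needs 140 minutes, not the stated 120, and group B's pre-to-post cortisol interval is 30 minutes longer than group A's

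*Protocol article*

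**What the plan says.** The Outcomes section of the Protocol article lists measures to protect the cortisol measurement. One is that "all saliva samples are collected between 2 PM and 4 PM". The same paragraph sets the timing relative to the session: "Saliva will be collected 30 minutes before and following the intervention". The Trial Design section says the same of all outcomes: "Outcome measures are gathered 30 minutes prior to and following each intervention session to assess immediate effects".

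Session lengths differ by group. Textbox 1 gives group A "Preliminary understanding and familiarization (10 minutes)Creation of traditional Chinese landscape paintings (25 minutes)Chinese calligraphy creation (15 minutes"). Textbox 2 repeats these three parts for group B and adds "Display and appreciation of artworks (5 minutes)Discussion of ongoing individual art activities (25 minutes"). The text on the combined intervention confirms the total: it "consists of an 80-minute integrated session led by a single researcher (RA").

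The Routine Care section puts both kinds of session in one slot: "The Chinese art activities and Chinese art activities with peer group participation interventions are planned from 2 PM to 4 PM". No separate start time is given for either group.

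The Statistical Methods section tests cortisol by paired t tests before and after the intervention within groups A and B, and by independent-sample t tests of each active group against control and of B against A. It includes no term for sampling time and rules out further analyses.

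**The concern.** The article fixes a clock-time window so that time of day does not disturb the cortisol values. Its other timing statements appear to defeat that window in group B, and they give the two active groups different intervals between the pre and post samples.

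If cortisol changes over the afternoon for reasons unrelated to treatment, two problems follow. A paired test within a group counts that change as an intervention effect. The comparison of B with A carries whatever part of the change belongs to the extra time in B. That comparison serves objective 3, which asks whether adding peer participation gives lower cortisol, and cortisol is the trial's only objective outcome.

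**Working it through.** **Inputs.** Session parts from Textboxes 1 and 2; window and sample timing from Outcomes and Trial Design; session slot from Routine Care.

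**1. Session lengths.**
- Group A: 10 + 25 + 15 = 50 min.
- Group B: 10 + 25 + 15 + 5 + 25 = 80 min, which reproduces the stated 80.

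**2. Span from pre to post sample** = lead + session + lag, against a window of 120 min.

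| Reading of the 30 minutes | Group A | Group B | B fits 120? | B − A |
|---|---|---|---|---|
| 30 before and 30 after (natural reading) | 30 + 50 + 30 = 110 | 30 + 80 + 30 = 140 | No, 20 over | 30 |
| 30 before, post sample at once | 30 + 50 = 80 | 30 + 80 = 110 | Yes | 30 |
| Pre sample at start, 30 after | 50 + 30 = 80 | 80 + 30 = 110 | Yes | 30 |

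In general, B fits only if lead + 80 + lag ≤ 120, that is, if lead + lag ≤ 40 min. The 3-minute film is described in the text but not listed in Textbox 1. Counting it as extra time gives 113 and 143 min in the first row, and the conclusion is the same.

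**3. Start times that satisfy the window on the natural reading.**
- The pre sample must be no earlier than 2:00 PM, so the session starts at 2:30 PM or later in either group.
- Group A's post sample must be no later than 4:00 PM: start ≤ 4:00 − 80 min = 2:40 PM. The feasible range is 2:30 to 2:40 PM.
- Group B's post sample must be no later than 4:00 PM: start ≤ 4:00 − 110 min = 2:10 PM, which contradicts 2:30 PM or later. No start time works.
- A session starting at 2:00 PM puts the pre sample at 1:30 PM in both groups, outside the window.

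**4. Difference between the groups.** With the same lead and lag, (lead + 80 + lag) − (lead + 50 + lag) = 30 min whatever the reading. With a common start, all 30 min fall on the post sample. For example, a 2:30 PM start gives post samples at 3:50 PM in A and 4:20 PM in B. With different starts, the pre and post clock times both move, but the interval is still 30 min longer in B.

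**5. What this does to the tests.** Suppose cortisol changes by β per hour with no intervention effect, linearly over the afternoon. On the natural reading:
- within-group change in A: β × 110/60 = 1.83β;
- within-group change in B: β × 140/60 = 2.33β;
- difference in change, B − A: β × 30/60 = 0.5β.

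The article gives no β. As an illustration only, if |β| were 0.1 to 1.0 nmol/L per hour (an assumption), 0.5|β| would be 0.05 to 0.5 nmol/L.

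**The case against.** **The 30 minutes may be loose.** The Outcomes sentence can be read as 30 minutes before and then directly after, or as within 30 minutes. Group B then fits. This stands: the impossibility holds only if a full 30 minutes applies on both sides. The 30-minute difference in interval does not depend on that reading.

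**Stronger readings that the document does not support.**
- *That group B's post sample is always 30 minutes later than group A's.* This needs a common start, which is not stated. If A's session ran after B's, A's post sample would be the later one.
- *That one research assistant delivering both sessions needs 50 + 80 = 130 min and so overruns the slot.* This assumes sessions in sequence. The article does not say so, and it leaves open a shared art phase for A and B. It also cannot be combined with a common start.
- *That the control group's samples have no anchor.* Table 1 marks usual care with pretest and posttest assessments at each session day, and Routine Care gives the control group's activity hours. Clock times by group may stand in the full protocol or in Figure 2, neither of which is shown, so their absence here is not a fault.
- *That objective 4 is also distorted.* PWB is measured only at enrollment and at T4, and T4 has no session. Post-session timing therefore need not enter the PWB part.

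**The bias may be small, and cortisol is one of five outcomes in a trial that calls itself exploratory.** This is fair as to weight. The sample size rests on loneliness, and a longer session is inherent in adding peer participation. But small size cannot be shown from the article either, and the authors themselves list sampling time among the things to control.

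**Conclusion.** The timing statements conflict. On the natural reading, group B's samples span 140 minutes against a 120-minute window, so at every such session at least 20 minutes of the span lie outside it. Group A complies only with a start between 2:30 and 2:40 PM. On looser readings the window can hold, but group B's pre-to-post interval remains 30 minutes longer, provided both groups use the same lead and lag.

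Because the planned t tests have no time term, any time-of-day change in cortisol is mixed with the effect they are meant to estimate. The within-group tests are the most exposed, since they have no comparator at all. How large this is, and which group it favours, cannot be determined from the article: that needs the actual clock times and the afternoon slope of cortisol. The point concerns the cortisol analyses only and should be corrected before results are reported.

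**What to change.** 1. Reconcile the timing in Trial Design, Textboxes 1 and 2, the description of the combined intervention, Routine Care and Outcomes. State the sampling window actually used and the pre and post clock times in each group, including control.
2. Keep the planned post-session cortisol contrasts, since immediate effects are the stated aim. Report each also with adjustment for collection clock time, or for the pre-to-post interval, where times were logged. If times were not logged, use scheduled times and show a range of assumed slopes. Data collection ended on October 31, 2025, so this must rest on existing records. The time-adjusted results should be labelled as added after data collection.
3. Do not read a within-group fall in cortisol as an intervention effect unless control samples over the same clock times show a smaller fall.

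The cost is a corrected paragraph, retrieval of collection times and one covariate. The drawback is wider intervals, because sampling time is partly collinear with group, so adjustment may separate the two only weakly. That uncertainty should be reported as it stands.

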### Statistical Methods

This study will use computer-based data analysis with the following statistical procedures.

After data collection is completed, the RA will review and remove any missing data. Before inputting the results into the computer to create a dataset, all data need to be checked, and errors need to be corrected. Descriptive statistics will be used to analyze and describe the demographic data of the participants.

In this study, the dependent variables are PWB, happiness, loneliness, relaxation, and salivary cortisol levels, and the independent variables are interventions (Chinese art activities, Chinese art activities+peer group participation, and routine care). Descriptive statistics will be used to check for missing values, out-of-range data, and data accuracy. Histograms, skewness, and kurtosis will be used to test the normality of the dependent variables in each group. If the data follow a normal distribution, the mean and SD will be used for analysis. If they are not normally distributed, the median and IQR will be used to represent them.

For the testing of objectives 1 and 2, a dual test of intra- and intergroup comparisons will be used. If the data are normally distributed, 2-tailed paired-sample *t* tests will be used for intragroup comparison of the Chinese art activities group or the Chinese art activities and peer group participation group. This will test the intervention effects of the Chinese art activities or Chinese art activities with peer group participation interventions on happiness, relaxation, loneliness, and salivary cortisol levels before and after the intervention (3 times). We will use independent-sample *t* tests to compare the effects of the Chinese art activities or Chinese art activities with peer group participation interventions on happiness, relaxation, loneliness, and salivary cortisol levels with the control group. For the testing of objective 3, an independent-sample *t* test will be used to compare the effects of the Chinese art activities with peer group participation and the Chinese art activities interventions on happiness, relaxation, loneliness, and salivary cortisol levels. For the testing of objective 4, salivary cortisol levels will be the main independent variable, and changes in PWB or relaxation will be divided into 3 quartiles as dependent variables. Ordered logistic regression analysis will be used to explore the association between salivary cortisol and these 2 variables. There will be no additional analyses.

Due to the harmless and short-term nature of this study, there will be very little missing data. Preliminary analysis will be conducted based on the complete case. We will use mean imputation for any missing data within a scale. Following the intention-to-treat principle, participants with intervention data will be included in the analysis.

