## Discussion

### Anticipated Findings

To our knowledge, this is the first exploratory study on the improvement effect of traditional Chinese art activities on PWB among individuals who are new residents of older adult centers. On the basis of our pilot study demonstrating the feasibility and potential of Chinese art activities and Chinese art activities with peer group participation, this multicenter RCT aims to provide preliminary evidence on the effectiveness of these interventions in institutional environments. By comparing the outcomes of both interventions, we expect to determine the best program that is suitable for individuals who are new residents of older adult centers. At the same time, we speculate that combining subjective scales with the objective indicator of salivary cortisol can effectively verify the positive effects of Chinese art activities and Chinese art activities with peer group participation and salivary cortisol will significantly correlate with the subjective results of PWB, which will further confirm the physiological basis for the effects of these interventions.

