### Limitations

The intervention in this study will be implemented 3 times with a duration of only 1 week. Although results will be measured 1 week later, the total study time does not exceed 1 month. This may not be a major limitation for exploration research, but it is far from enough to expect long-term results. In addition, a short-term intervention is not conducive to the establishment of peer relationships. This may lead to the correctness of the relevant research results, which needs to be taken into account when interpreting the research results at the later stage in an actual RCT. It is recommended that future studies extend the duration to at least 3 months.

In our data collection process, VASs will be used for happiness, loneliness, and relaxation before and after the interventions. This repeated measurement in a short period can easily lead to practice effects and response shifts, resulting in measurement bias and a decrease in experimental validity. Therefore, when interpreting the data in this study, it is necessary to fully consider this limitation.

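### Objectives 1 and 2 are tested partly by before-after t tests inside the active arms, which cannot isolate an intervention effect, and no rule says what happens if they disagree with the randomised comparison

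*Protocol article*

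**What the plan says.** The article randomises participants 1:1:1 to group A (art activities), group B (art activities plus peer group participation) and group C (routine care). Under Statistical Methods it states: "For the testing of objectives 1 and 2, a dual test of intra- and intergroup comparisons will be used".

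- **Within-arm half.** If the data are normal, "2-tailed paired-sample *t* tests will be used for intragroup comparison of the Chinese art activities group" or of the combined group. The text says these tests assess the interventions' effects "on happiness, relaxation, loneliness, and salivary cortisol levels before and after the intervention (3 times").
- **Between-arm half.** "We will use independent-sample *t* tests to compare the effects of the Chinese art activities or Chinese art activities with peer group participation interventions" with control on the same four outcomes. The number of occasions is not given.
- **Objective 3.** "For the testing of objective 3, an independent-sample *t* test will be used", comparing B with A on the same outcomes.

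The section closes the list by saying that no further analyses will be done. It does not say whether both halves must be significant, or which one decides. The Limitations section says of the repeated VAS ratings: "This repeated measurement in a short period can easily lead to practice effects and response shifts". Three of the four tested outcomes are VAS scores. Five dependent variables are listed and none is called primary. The only significance level given, .05, is in the Sample Size section.

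**The concern.** A paired test compares an arm with itself. It answers whether scores moved between the pre and post measurement, not whether the intervention moved them. Anything else that acts over the same interval is counted as effect: sitting through an afternoon activity period, growing used to the scale, or reinterpreting it. The trial has a randomised control arm precisely to remove such influences, and the comparison with that arm is the valid evidence for objectives 1 and 2.

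As written, the within-arm test has the same standing as the randomised one. If scores improve similarly in all three arms, the paired tests can be significant and the between-arm tests not, and the text leaves open whether the objective is then met. This matters beyond the data table. Under Anticipated Findings the article says "we expect to determine the best program that is suitable for individuals who are new residents of older adult centers", and the Dissemination Plan foresees practical guidelines for care institutions.

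**Working it through.** The plan states no error rate for this two-part test, so there is no figure of its own to reproduce. The check asks how each half behaves when the intervention does nothing.

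**1. Inputs.**
- From the article: 30 per arm (90 in three equal arms), two-tailed tests, alpha .05, four outcomes, three sessions, two active arms.
- Assumed: a drift shared by all arms of 0.2, 0.3 or 0.5 SD, and a pre-post correlation ρ of 0.5. The article gives neither.

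**2. Paired test under pure drift.** The standardised mean change is dz = drift / √(2(1 − ρ)). With ρ = 0.5 the divisor is 1, so dz equals the drift. The noncentrality is dz·√30.

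| Shared drift (SD) | dz·√30 | P(paired test significant), n = 30 | n = 24 (20% dropout) |
|---|---|---|---|
| 0.2 | 1.10 | 0.185 | 0.156 |
| 0.3 | 1.64 | 0.355 | 0.291 |
| 0.5 | 2.74 | 0.754 | 0.650 |

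The result depends on ρ. At n = 30 the three values are 0.15, 0.27 and 0.61 for ρ = 0.3, and 0.28, 0.54 and 0.93 for ρ = 0.7.

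**3. Between-arm test under the same drift.** The drift is in both arms and cancels in the difference. In simulation the rate stays at about 5% for every drift.

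**4. If both halves had to be significant.** Simulated with a drift of 0.3 or 0.5 SD and no intervention effect, a single arm, outcome and session passes both tests about 2.5% to 2.9% of the time. Under that rule the paired test would not inflate the error of a single comparison. The rule is not written.

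**5. Number of tests (secondary).**
- Paired: 4 outcomes × 3 sessions × 2 arms = 24.
- Between-arm, including objective 3: 3 contrasts × 4 outcomes = 12 if run once, or 12 × 3 = 36 if run per session.
- Total: 36 to 60, before the two regressions for objective 4.

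**6. Chance of at least one false positive among the between-arm tests at .05.** If they were independent, it is 1 − 0.95^12 = 0.46 for 12 tests and 1 − 0.95^36 = 0.84 for 36. These are upper figures, because the contrasts share arms and the outcomes are likely to be correlated. Simulation with shared arms gives about 0.40 (12 tests) and 0.79 (36 tests) with uncorrelated outcomes. With an assumed correlation of 0.5 between outcomes and sessions it gives about 0.36 and 0.62 to 0.66.

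**The case against.** The best defence is that the randomised contrasts are already planned for the same four outcomes, and that a two-part test may mean both parts must agree. If so, step 4 shows no inflation per comparison. This stands in part: a reader might take 19% to 75% as the trial's false-efficacy rate, and the document does not support that. Those figures describe the paired test alone, under assumed drifts, and become false claims only if that half may count by itself. What remains is that the text calls the paired tests tests of the interventions' effects and gives no rule that prevents this.

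Four other stronger readings also fail.

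- **That control-arm drift is hidden.** Table 1 schedules pre and post assessments at each session, including for usual care, and Statistical Methods describes outcomes by group. The control values exist and can be reported; only a control-arm test is absent.
- **That the plan fixes some 60 tests.** The mention of three times belongs to the paired tests. The number of occasions for the between-arm tests is not stated, so 36 is equally open.
- **That carry-over between sessions adds to false efficacy.** Benefit carried into a later pre-session score would shrink the within-session change, which works the other way.
- **That loneliness must be primary because the sample was sized on it.** It was used as the most conservative of three available effect sizes, and the stated aim concerns psychological well-being.

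The article also calls the trial exploratory and speaks of preliminary evidence, and multiplicity rules may sit in an analysis plan that is not shown. That softens the multiplicity point. It does not make a within-arm test valid evidence of an intervention effect, and an analysis plan could remove that test only by contradicting the article.

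**Conclusion.** The narrow point holds with high confidence, because it is in the text: before-after tests inside the active arms form part of the test of objectives 1 and 2, they cannot separate the intervention from drift, and no rule settles a conflict with the randomised comparison. For scale, a shared drift of 0.2 to 0.5 SD would make a paired test significant about 19% to 75% of the time with no intervention effect (30 per arm, ρ = 0.5). Drift and correlation are assumptions; the article concedes that practice effects and response shifts can occur but gives no size.

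The multiplicity point is secondary and held with lower confidence. With no primary outcome and only the .05 level to go by, the upper figure for at least one false positive among the between-arm tests is 46% to 84%, depending on an occasion count the article leaves open. This supports reporting the results as exploratory. It does not establish that the plan is obliged to adopt a particular primary outcome or adjustment.

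**What to change.** 1. Reword Statistical Methods so that objectives 1 and 2 are judged only on A vs C and B vs C, and state on which occasion or occasions those contrasts are tested.
2. Replace the paired t tests by a descriptive table of pre-post changes in all three arms, with no p values.
3. Report the between-arm results as exploratory estimates with confidence intervals. If a primary outcome or multiplicity rule is wanted, fix it before the blinded analysts learn the allocation and disclose that it was set after data collection, which ended on October 31, 2025.

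The cost is a wording change and fewer nominally significant results. No new data are needed, since control-arm pre and post assessments are already scheduled.
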